#### Withdrawal of patients from the study and use of collected data in emergency situations:

- If the patient refuses to give post hoc consent, he/she will be withdrawn from the study and the data collected so far will not be used for the study purposes.
- If the representative refuses to give proxy consent, the patient will be withdrawn from the study and the data collected so far will no longer be used for the study purposes.
- If a patient dies before it has been possible to obtain a consent or refusal from the representative and in the absence of a statement of wishes, his/her data collected up to the death will be used for study purposes (without oral consent from a next of kin or designated trusted person ; waiver to ClinO Art 16, alinea 2). This would prevent biasing the study validity (a mortality rate of about 30% is anticipated in view of the clinical situation of the recruited patients (see 11.2).

## **2.8 Participant privacy and confidentiality**

The investigator affirms and upholds the principle of the participant's right to privacy and that they shall comply with applicable privacy laws. Especially, anonymity of the participants shall be guaranteed when presenting the data at scientific meetings or publishing them in scientific journals.

Individual subject medical information obtained as a result of this study is considered confidential and disclosure to third parties is prohibited. Subject confidentiality will be further ensured by utilising subject identification code numbers to correspond to treatment data in the computer files.

For data verification purposes, authorised representatives of the sponsor-coordinating investigator or an ethics committee may require direct access to parts of the medical records relevant to the study, including participants' medical history.

## **2.9 Early termination of the study**

The sponsor-coordinating investigator may terminate the study prematurely according to certain circumstances, for example:

- insufficient participant recruitment,
- alterations in accepted clinical practice that make the continuation of a clinical trial unwise,
- early evidence of benefit or harm of the experimental intervention

## **2.10 Protocol amendments**

Only the sponsor-coordinating investigator is allowed to amend the protocol. Local investigators may provide suggestions for a protocol amendment to the sponsor-coordinating investigator. Important protocol modifications will be submitted for approval to the lead CEC by the sponsor-coordinating investigator. Substantial amendments will only be implemented after approval of the CEC.

Under emergency circumstances, deviations from the protocol to protect the rights, safety and well-being of human subjects may proceed without prior approval of the sponsor-coordinating investigator and the CEC. Such deviations shall be documented and reported to the sponsor-coordinating investigator and the lead CEC as soon as possible.

All non-substantial amendments will be communicated to the lead CEC within the Annual Safety Report (ASR).

### 3. BACKGROUND AND RATIONALE

#### 3.1 Background and Rationale

Electroencephalography (EEG) is a non-invasive tool to monitor the electrical correlates of brain function with a high temporal resolution. First described almost 90 years ago, it has experienced an impressive development in the last couple of decades following digitalization (software), the coupling with video recordings, and the exponential increase of hardware memory, allowing prolonged recordings and a straightforward and easy to apply application in clinical practice. In fact, it represents one of the most broadly used diagnostic tools in the neurology field: as an example, in 2015 at the CHUV, 2600 EEGs were performed, versus 1700 electro-neuro-myography (ENMG) and 1300 ultrasound (Doppler/Duplex) studies.

In the last decade, continuous video-EEG monitoring (cEEG), designating the EEG recording over several hours or days typically coupled with concomitant video recording and algorithms allowing quick interpretation of compressed recording times, is increasingly used in the intensive care units (ICUs), especially in North America. The ICUs represent an environment related to considerable potential morbidity and mortality due to underlying critical diseases, not only involving primarily the brain, such as severe brain trauma, intracranial hemorrhage, subarachnoid hemorrhage, or ischemic stroke, but also in case of secondary brain injury, for example in patients with post-cardiac arrest encephalopathy, delirium, or sepsis-related encephalopathy. The role of cEEG mostly resides in identifying seizures and status epilepticus (SE; i.e., prolonged seizures), which often do not show specific clinical correlates in this particular clinical setting and may induce secondary brain injury, or to monitor treatment in patients with SE requiring general anesthesia for treatment. Furthermore, it is also possible to detect changes in the cerebral electrical activity heralding blood flow variation, for example with vasospasms following subarachnoid hemorrhage.

The American Clinical Neurophysiology Society has updated its recommendation for reporting particular EEG features in this setting, such as periodic and rhythmic patterns, contributing to a uniform nomenclature that should improve generalizability and inter-institutional comparability; they have been recently validated.

In the last three years, the European Society of Intensive Care Medicine (ESICM) and the American Clinical Neurophysiology Society published consensus statements intended to be guidelines regarding the use of cEEG (including, as a mandatory tool, video-correlation) in ICUs. cEEG video-monitoring is recommended for most patients with altered consciousness, in order to assist SE treatment management, especially in forms requiring pharmacological coma, and to rule out nonconvulsive seizures in brain-injured, or comatose patients with unexplained and altered consciousness. The North American guidelines further suggest its use in subjects with reduced level of consciousness under sedation or pharmacologically induced coma. cEEG should be recorded at least for 24 hours and interpreted at least twice daily. However, especially in the European publication, the authors recognize that the supporting evidence is generally low, and that additional data are clearly necessary.

Some years ago, it has been shown that cEEG influences clinical practice inducing changes in patients' treatments, and recent evidence suggests that the patients' amount of time spent in the ICU having electrographic seizures, in other words the seizure "load", correlates with prognosis both in children and adults. However, no study has yet determined whether this finding simply reflects a more severe brain damage / dysfunction by the underlying etiology, or it is directly and causally related to outcome. In particular, to the best of our knowledge, it remains unclear if cEEG leads to a better prognosis in specific patients' populations; this represents a central unanswered question for clinical purposes. To date, only one population-based study relying on US discharge diagnoses, and therefore probably challenged by a considerable imprecision, has suggested that cEEG does improve outcome, with an odds ratio of 0.63 for in-hospital mortality (95% confidence interval; 0.51-0.76;  $p < 0.001$ ).

On the one hand, cEEG has a clearly superior sensitivity in uncovering seizures and SE as compared to routine spot video-EEG (rEEG, which typically lasts 20-30 minutes): a seminal retrospective study in an ICU-based population showed that the detection rate doubles from round 50% after one hour of recording to 95% after 48 hours, especially in comatose subjects. Further evidence for the diagnostic yield of cEEG in patients with altered consciousness comes from a study revealing an increased detection rate of nonconvulsive SE after the introduction of cEEG as compared to historic controls with rEEG (monthly detection rates with cEEG  $5.44 \pm 1.33$ ; with rEEG  $2.17 \pm 1.89$ ,  $p=0.002$ ). Nevertheless, cEEG is a time- and resource consuming procedure, requiring skilled technical personnel, regular assessments by electroencephalographers, and ideally the availability of dedicated, portable video-

EEG recording machines that may be connected to the hospital network for out-of-site inspection, as well as specially conceived supplies allowing emergent imaging procedures (e.g., computed tomography- and magnetic resonance imaging compatible electrodes), namely overnight. Practical considerations have emerged in recent years. For example, it seems that a refined analysis of the first part of cEEG may allow stratifying the risk of encountering seizures in the subsequent recording: if no epileptiform discharge is detected in the first 30-120 minutes, the likelihood would be below 5%. Also, the use of automated software allowing the interpretation of compressed EEG seems to clearly improve efficacy in this setting, reducing the time required to analyze a cEEG by 78%, with minimal loss of sensitivity. While large, mostly academic centers in North America have been using cEEG increasingly since the turning of the century, the vast majority of European hospitals - and all Swiss hospitals including university centers - still do not have the resources to apply cEEG to all patients with consciousness impairment in- or outside the ICUs, and therefore, disturbingly, are not complying with the current European guidelines.

### **3.2 Investigational Product (treatment, device) and Indication**

Continuous and routine video-EEG will be performed with recording machines normally used in clinical practice in the participating hospitals; for information, EEG is used in Swiss hospitals since the 1940's, and continuous EEG since at least 15-20 years; video-EEG are routinely used since more than 10 years. To offer an idea of its frequency, there are between 1500-4000 yearly EEG studies in each participating hospital.

EEG recording and interpretation machines by different manufacturers will be used: Lausanne, Bern, Basel and Sion rely on the Nicolet system (Viasys, Neurocare, Madison, WI), while Geneva uses Micromed devices (Mogliano Veneto, TV, Italy). Persyst, Version 13 (San Diego CA), an automated EEG array display is used in the different participating centres (routinely in Lausanne and Sion).

Data for quantitative analyses will be exported in EDF+ format (readable with Matlab and other research softwares).

### **3.3 Preclinical Evidence**

Not applicable

### **3.4 Clinical Evidence to Date**

As mentioned above, only one US population-based study suggested that cEEG does improve outcome, with an odds ratio of 0.63 for in-hospital mortality (95% confidence interval; 0.51-0.76;  $p <$

0.001).

The use of cEEG in postanoxic patients was addressed recently by the team of the Sponsor-coordinating investigator: in this particular diagnostic category the yield of cEEG seems comparable to that of a repeated rEEG. In this study, in fact, the blinded review of 34 cEEG that were transformed post-hoc to 2 rEEG “clipped” each at the time of reactivity testing showed a comparable performance to that of the whole trace. Despite a relatively limited sample size, this represents a rationale to optimize the EEG use in resource-limited hospitals.

More recently, the same team retrospectively collected 29 consecutive patients with non-convulsive SE without coma, undergoing extended EEG; these were compared to an historical age-matched group of 58 patients managed with routine EEG only. While SE severity was similar in the two groups, with similar proportion of potential fatal etiologies (58% in the extended EEG group vs 60%,  $P=.529$ ), and comparable acute hospitalization duration (median of 15 vs 11 days,  $P=.131$ ), the extended EEG group received slightly more anti-epileptic drugs (median was three in both groups,  $P=.026$ ). Distribution of the outcome categories at hospital discharge did not show any statistical difference ( $P=.129$ ) (*Eskioglou et al., Acta Neurol Scand, in press*).

### **3.5 Dose Rationale / Medical Device: Rationale for the intended purpose in study (pre-market MD)**

The time frame of 30-48 hours for cEEG and rEEG derives from the seminal study by Claassen et al, showing that within this time lapse the vast majority of seizures are detected in critical care patients.

### **3.6 Explanation for choice of comparator (or placebo)**

Routine practice in the vast majority of European (and Swiss) hospitals, to date, is to perform rEEG. It is also common practice to repeat rEEG in several clinical situations. Therefore, 2 rEEG were chosen as the (standard) comparator.

### **3.7 Risks / Benefits**

Since the EEG is a noninvasive procedure, there are no significant risks that will be associated with either rEEG or cEEG. The only potentially challenging issue is a skin reaction under the electrodes in patients undergoing cEEG, which is extremely uncommon before seven to ten days of uninterrupted recording. The participating centers, however, are currently already recording each year many cEEG in the proposed clinical setting, and skin reactions virtually never represent a problem for patients, and may be easily treated with local applications.

All files and records will be coded; therefore, there will be no risk of disseminating patients' identities. All study members will be submitted to strict confidentiality, according to current Swiss laws.

As a positive collateral effect of participating in the study, it is to expect that patients will tend to be followed up more carefully than in routine clinical practice.

There will be no blinding of the procedure to treating physicians and electroencephalographers. Such a blinding in this particular clinical setting would imply having two separate teams of clinical neurophysiologists in each center, which seems highly impractical. Furthermore, withdrawing EEG information to the treating team would not only raise ethical questions, but also potentially impact on the clinical outcome at 6 months, therefore biasing the study. Importantly, in order to minimize confounding by EEG allocation (information bias), we foresee to assess at 6 month the primary and several secondary outcomes in a blinded fashion using a recently proposed structured interview for the functional outcome.

### **3.8 Justification of choice of study population**

This study can by definition only be conducted in patients with altered mental state (see background), therefore not capable of judgment. It is in fact impossible to extrapolate findings from patients without altered mental state, as these in the vast majority of case do not need EEG for detection of seizures.

This study involves the use of EEG in an acute setting: it is not possible to postpone the procedure in order to await consent by the patient or legal representative if the latter is not readily available, as this is needed for clinical reasons.

The consent procedure in this emergency setting is already described under 2.7

## **4. STUDY OBJECTIVES**

### **4.1 Overall Objective**

The present study intends to assess if EEG signals, recorded continuously or intermittently, have a prognostic impact in patients with altered consciousness.

### **4.2 Primary Objective**

The primary objective is to assess if cEEG offers advantages over rEEG in adult patients with altered consciousness in terms of survival at 6 months.

### **4.3 Secondary Objectives**

The secondary objective is to assess if cEEG versus rEEG offers advantages in terms of functional outcome, seizure detection rate, hospital infections rate, need and duration of mechanical ventilation, length of stay and costs.

### **4.4 Safety Objectives**

NA

## **5. STUDY OUTCOMES**

### **5.1 Primary Outcome**

- Mortality at 6 months (frequency).

### **5.2 Secondary Outcomes**

- Functional outcome at four weeks and at six months (evaluated using the modified Rankin Scale (mRS), and the Cerebral Performance Categories (CPC) , ordinal),
- Evaluation at 4 weeks and 6 months of the ability to go back to work/school if previously working/at school (proportion),
- Seizure/SE detection rate, and time to detection after the start of EEG recording, and presence of concomitant clinical signs of seizures (proportion, resp. continuous variable)
- Detection of interictal potentially epileptiform features (spikes, spike and waves, sharp waves, isolated or repeated at <3Hz without any evolution; lateralized rhythmic delta activity  (proportion),
- Rate of in-hospital infections requiring antibiotic treatment at 4 weeks after first EEG (proportion),
- Need and duration of mechanical ventilation at 4 weeks after first EEG (proportion, resp. continuous variable),
- Duration if ICU and hospital stay (continuous variable),
- Patient destination after acute facility (home, rehab, nursing home, other; categorical)
- Change in clinical patient management (i.e., antiepileptic drugs (AED) introduced or stopped, AED increased or decreased, brain imaging procedure order) occurring during the 60 hours following the start of the first EEG (categorical).
- Correlation between quantitative EEG analysis and outcome.

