### **5.3 Other Outcomes of Interest**

- Global hospitalization costs intended as amount billed for each patient's acute hospital stay, assessed through the billing department of each hospital (continuous variable – stratified by site).

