## **6. STUDY DESIGN**

### **6.1 General study design and justification of design**

This will be a multicenter randomized controlled trial assessing prognostic yield of cEEG. While there will be no blinding during the EEG procedure, as this would prove highly impractical in the proposed setting; however, the most important outcomes will be assessed blindly (at 6 month). The study will be carried out in four university hospitals (of the five in Switzerland) and one large regional hospital, located both in the German- and the French-speaking part of the country. An RCT seems the best way to address the primary objective of this study, particularly in terms of minimization of biases.

It is expected to randomize 350 patients over a 2 year-recruiting period. Patients will receive either cEEG or 2 rEEG within the first 48 hours following randomization, and then will be followed up until 6 months after randomization.

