### 9.2.2. Assessment of secondary outcomes

The following secondary outcomes will be assessed. Of note, the assessments at 4 weeks will be done through chart review or by phone to the patient, representative or general practitioner, depending on the patient's medical condition, consent status and location. All secondary outcomes at 6 months will be assessed through a structured phone interview (to the patient, representative or general practitioner, depending on the patient's medical condition, consent status and location) by a study team member blinded to the EEG intervention.

- Functional outcome (modified Rankin Scale (mRS), Cerebral Performance Categories (CPC), ordinal), assessed at 4 weeks through chart review or phone and at 6 months through structured phone interview.
- Back to work/school if previously working/at school, assessed at 4 weeks through chart review or phone and at 6 months through structured phone interview.
- Seizure/SE detection rate, and time to detection after the start of EEG recording, and presence of concomitant clinical signs of seizures, assessed through chart review at 48hours.
- Detection of interictal potentially epileptiform features (spikes, spike and waves, sharp waves, isolated or repeated at <3Hz without any evolution; lateralized rhythmic delta activity (proportion)), assessed through chart review at 48hours.
- Rate of in-hospital infections requiring antibiotic treatment assessed at 4 weeks through chart review.
- Need and duration of mechanical ventilation, assessed at 4 weeks through chart review.
- Duration of ICU and hospital stay, assessed at 4 weeks through chart review.
- Patient destination after acute facility, assessed at 4 weeks through chart review or phone and at 6 months through structured phone interview.
- Change in clinical patient management (i.e., AED introduced or stopped, AED increased or decreased, brain imaging procedure order) occurring during the 60 hours following the start of the first EEG (categorical), assessed through chart review at 48-60 hours.
- Correlation between quantitative EEG analysis and outcome assessed, assessed at the study end by the Bern team in a blinded fashion.

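### Counting management changes, length of stay, infection and ventilation from randomisation, and adjusting the bill for earlier days, would be a cheap improvement to the secondary outcomes

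*Protocol*

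**What the plan says.** Protocol section 5.2 defines management change (antiepileptic drugs started, stopped or altered in dose, or brain imaging ordered) as a change "occurring during the 60 hours following the start of the first EEG". Section 9.2.2 repeats this and places the chart review at 48-60 hours. The study schedule puts that review in the T48-T60 column, with a visit window of +24 h.

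Ventilation is listed as "Need and duration of mechanical ventilation at 4 weeks after first EEG", and infection needing antibiotics carries the same 4-week time point. Length of stay appears in section 9.2.2 as "Duration of ICU and hospital stay, assessed at 4 weeks through chart review"; no start is given. Section 5.3 defines cost as "Global hospitalization costs intended as amount billed for each patient's acute hospital stay".

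On timing, section 6.1 says "Patients will receive either cEEG or 2 rEEG within the first 48 hours following randomization" and sets follow-up at 6 months from randomisation. Sections 6.2.1 and 7.3 place randomisation immediately before the EEG. The schedule lists randomisation in the T-5 to T0 column and starts the intervention period at T0, but nowhere states which of the two events T0 is. Section 11.5 recognises randomised patients in whom the intervention never began. It classes them as dropouts and replaces them.

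**The concern.** The analysis compares groups by allocation. Such a comparison is cleanest when every outcome is counted from a moment that exists for each randomised patient and cannot depend on the arm. Randomisation is that moment; the start of the first EEG is not. The trial is open label, and setting up a continuous recording may take a different time from setting up a spot recording. A patient whose EEG never starts has no 60-hour window at all.

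For stay and bill the issue is precision. Eligible patients are in-patients, with no limit on days since admission. Days and charges before randomisation cannot respond to either arm, so including them blurs whatever difference exists afterwards.

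**Working it through.** **Plan's own figure.** The protocol gives no figure for these windows. Its sample size reproduces: with 61% and 75% survival, two-sided alpha 0.05 and power 0.80, n = [1.96·√(2·0.68·0.32) + 0.8416·√(0.61·0.39 + 0.75·0.25)]² / 0.14² = 173.1, so 174 per arm and 348 in all. Nothing below changes it.

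**1. Management change: the two clocks.** If T0 is randomisation and the EEG starts d hours later, the 60-hour window closes at T0+60+d. A review at T48 cannot cover it. A review at T60 covers it only if d = 0; otherwise it depends on the +24 h visit window. If T0 is instead the EEG start, a review before T60 is still too early.

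**2. Management change: how large d may be.** Inputs: all study EEG within 48 h of randomisation (6.1); cEEG of at least 30 h, and two rEEG over 24 to 48 h (8.1).
- cEEG: 48 − 30 = 18 h at the latest.
- rEEG: 48 − 24 = 24 h at the latest, reading section 8.1 as at least 24 h between the two. The synopsis says within 30-48 hours, so this is one reading.

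These are outer limits, not expected delays.

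**3. Management change: what a difference in delay could do (illustration only).** Assume no true effect, 174 per arm, 30% or 50% of patients with a change within 60 h of randomisation, and an event hazard that halves every 24 h. In an arm whose EEG starts d hours later than in the other, the proportion counted becomes 1 − (1 − p)^(2^(−d/24)).

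| Between-arm delay | Spurious difference (points) | False-positive rate |
|---|---|---|
| 1 h | 0.7 to 1.0 | about 5% |
| 3 h | 2.1 to 3.0 | 7% to 9% |
| 6 h | 4.1 to 5.8 | 14% to 19% |
| 12 h | 7.7 to 11.3 | 38% to 57% |

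Counting from randomisation gives 0 points and 5% in every row. The documents do not say which row applies.

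**4. Stay and bill.** With pre-randomisation SD s0, post-randomisation SD s1 and independence, variance is multiplied by 1 + (s0/s1)². None of these SDs is in the protocol. Assuming s1 = 10 days:
- s0 = 3: 1 + 0.09 = 1.09. As information, 348/1.09 ≈ 319 patients. A comparison with 80% power falls to Φ(2.80/√1.09 − 1.96) ≈ 77%.
- s0 = 5: 1 + 0.25 = 1.25. 348/1.25 ≈ 278 patients, and power falls to Φ(2.80/√1.25 − 1.96) ≈ 71%.

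The 348 was set for mortality and is used here only to give scale.

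**5. Infection and ventilation.** A 6 h shift is 6/672 = 0.9% of 28 days, and 12 h is 1.8%. The Week 4 visit itself may move by ±4 days. The anchor in hours is immaterial. What is open is whether infection or ventilation already present at randomisation counts.

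**The case against.** The strongest reply is that the protocol nearly closes the gap. Randomisation comes immediately before the EEG in both arms, so first EEG and T0 should almost coincide, and at a 1 h difference the error rate stays near 5%. That stands, and it is why a reader should not infer that the 60-hour comparison is biased in practice. The 18 h and 24 h limits are theoretical, and no document gives a between-arm gap.

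Three other strong readings are tempting and not supported:
- That the infection and ventilation windows shift with the arm. Section 5.2 fixes when they are read, not where counting begins, and hours are negligible over four weeks.
- That stay and bill are biased. Randomisation balances earlier days between arms; they add noise only. Inclusion of the whole stay is explicit for the bill and merely the natural reading for length of stay.
- That the first EEG might be one done before the study. The control arm has two recordings, which sufficiently explains the word first.

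It can also be said that counting from the EEG captures decisions that follow EEG information, while counting from randomisation admits some that no EEG could have influenced. This is true and is the price of the change. It is a small dilution open to both arms alike, whereas the EEG start can differ by arm.

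Non-starters are already replaced under section 11.5. Whether that suits an analysis by allocation is a separate question, but replacement does not give those patients a window. Finally, the details of a duration variable may sit in an analysis plan. That is fair for stay, but the 60-hour start and the whole-stay bill are fixed in the protocol itself.

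**Conclusion.** The point holds as a cheap improvement to secondary and other outcomes. The clearest part is the 60-hour management-change window. It starts at an unblinded post-randomisation event that some randomised patients never reach, and it does not fit the T48-T60 review. Any shift between arms should usually be small but is bounded only by the 48-hour limit.

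For stay and bill the cost is avoidable variance: 9% to 25% under assumed SDs of 3 to 5 days before and 10 days after randomisation, independent of each other. For infection and ventilation the gain is only the exclusion of events and days before randomisation. The mortality analysis and the 348 patients are untouched.

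**What to change.** In sections 5.2, 5.3 and 9.2.2 and the schedule:
- State that T0 is randomisation.
- Count management changes from T0 to T0+60 h, and collect them once 60 h have passed. Since study EEG falls within 48 h of randomisation, this window holds the whole intervention plus at least 60 − 48 = 12 h in both arms.
- Count ICU/intermediate-care days and hospital days from randomisation to discharge.
- Keep the whole-stay bill, but adjust its comparison for days from admission to randomisation. The planned multivariable models do not name this covariate.
- Count new infections and ventilation days from randomisation to Day 29.

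The cost is protocol wording and date arithmetic: admission and discharge times are on the schedule, and randomisation is logged by the web system. The downside is that a few decisions made before the EEG are counted in both arms.
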